# Implementing an exercise intervention for sarcopenia in oldest-old nursing home residents: protocol for a pragmatic cluster-randomized controlled trial (SCOPE Study)

**DOI:** 10.1186/s12877-026-08002-8

**Published:** 2026-08-31

**Keywords:** Sarcopenia, Oldest-old, Baduanjin, Resistance training, Nursing home, Pragmatic randomized controlled trial

## Abstract

**Background:**

Sarcopenia is a progressive age-related condition characterized by loss of muscle mass, strength, and function, with particularly high prevalence among nursing home residents and the oldest-old population. Although exercise is a recognized non-pharmacological intervention, existing evidence has largely been generated in selected community-dwelling populations, limiting its applicability to vulnerable older adults in real-world long-term care settings. The SCOPE study (Sarcopenia Care in Oldest-old: a Pragmatic Exercise cluster-randomized controlled trial) evaluates the effectiveness and feasibility of caregiver-led modified Baduanjin, resistance training, and combined exercise interventions for sarcopenia management in nursing home residents.

**Methods:**

This pragmatic, cluster-randomized controlled trial aims to recruit 104 residents aged ≥ 75 years with sarcopenia from a large nursing home in Hangzhou, China. Participants will be randomized by residential building into four groups: Modified Baduanjin Group, Resistance Training Group, Combined Exercise Group, and Control Group. The 48-week intervention will be delivered by trained caregivers using video-guided sessions, with phased reduction in specialist supervision. The primary outcome is a composite sarcopenia Z-score integrating handgrip strength, Short Physical Performance Battery, and appendicular skeletal muscle mass index. Secondary outcomes include functional mobility, balance, physical activity and sedentary behaviour, neuromuscular activation, questionnaire-based assessments, and saliva biological markers. Clinical events and care-dependency records will also be collected throughout the intervention and follow-up periods. Assessments will be conducted at baseline, week 12, week 24, week 48, and at 1 and 2 years post-intervention.

**Discussion:**

The SCOPE study addresses the need for feasible and sustainable exercise interventions for sarcopenia in real-world nursing home settings. By integrating pragmatic caregiver-led delivery, multimodal outcome assessment, and long-term follow-up, this trial aims to inform exercise prescription, implementation feasibility, and potential mechanisms of adaptation in oldest-old nursing home residents. The findings are expected to support the development of scalable exercise intervention frameworks for sarcopenia management in long-term care facilities.

**Trial registration:**

Chinese Clinical Trial Registry (ChiCTR2500107315).

**Supplementary Information:**

The online version contains supplementary material available at https://doi.org/10.1186/s12877-026-08002-8.

## Background

Sarcopenia is a progressive, age-associated condition characterized by a decline in skeletal muscle mass, strength, and function, a combination that substantially increases the risks of frailty, falls, disability, and mortality [1]. This progressive loss of muscle tissue is estimated to result in up to a 40% reduction in muscle mass between the ages of 20 and 70, with the rate of decline accelerating to approximately 1.4%–2.5% per year after the age of 60 [2]. This age-related decline extends beyond muscle quantity, as muscle strength and physical performance have likewise been shown to deteriorate in a largely linear manner with advancing age [3]. At the population level, this condition affects approximately 10%–16% of older adults worldwide [4], indicating a substantial public health burden. This burden, however, is not evenly distributed across care settings. Evidence from a meta-analysis of 34,955 participants demonstrates that prevalence rates are markedly higher among nursing home residents, reaching 51% (95% CI: 37–66%) in men and 31% (95% CI: 22–42%) in women, whereas substantially lower estimates have been reported among community-dwelling individuals, at 11% (95% CI: 8–13%) in men and 9% (95% CI: 7–11%) in women [5].

With the continued extension of global life expectancy [6], the burden of sarcopenia has increasingly shifted toward adults aged 80 years and above, a population that experiences more pronounced functional decline and a substantially elevated risk of sarcopenia-related adverse events. This concentration of disease burden in the oldest-old, however, is not adequately reflected in the existing evidence base, as most randomized controlled trials (RCT) evaluating behavioral interventions for sarcopenia have been conducted predominantly in relatively younger older adults, typically between 55 and 75 years of age [7, 8]. This mismatch between disease burden and study populations may consequently limit the applicability and clinical relevance of current findings for the oldest-old.

Among modifiable risk factors, physical inactivity has been identified as a key contributor to the development and progression of sarcopenia, primarily through its association with muscle atrophy and functional deterioration [9, 10]. Given this central role, increasing physical activity (PA) has emerged as one of the most effective non-pharmacological strategies to counteract sarcopenia. This therapeutic value is supported by a growing body of evidence, which demonstrates that structured exercise interventions can significantly improve muscle strength, muscle mass, and functional performance in older adults [7, 11–13]. On the basis of this evidence, current clinical guidelines place PA at the core of both sarcopenia prevention and management, particularly in light of the limited availability of effective pharmacological treatments [14, 15].

Resistance training is widely regarded as the cornerstone of exercise-based interventions for sarcopenia [16]. In practice, however, its application among frail or institutionalised older adults is frequently constrained by safety concerns, joint stress, and space limitations [17], underscoring the need for alternative or complementary exercise modalities. In this context, mind–body exercises such as Tai Chi and Baduanjin, which are traditional Chinese practices characterised by slow, flowing movements integrated with breathing and mental focus, have attracted growing interest. Evidence suggests that these low-impact exercises confer benefits across multiple domains, including mental well-being [18], cognitive function [19], balance [20] and physical performance [21] in older adults. Their safety and acceptability, even among frail individuals [22], further highlight their potential value, particularly in promoting neuromuscular coordination [23]. Among these modalities, Baduanjin may be particularly relevant for sarcopenia management because it consists of a limited number of standardised movements, requires no special equipment, imposes relatively low mechanical stress on the joints, and integrates breathing regulation and attentional focus with coordinated trunk and limb movements, postural control, and neuromuscular coordination [24]. Recent RCTs have provided preliminary direct evidence supporting its potential value in sarcopenia management, reporting improvements in physical performance, balance, lower-limb strength, skeletal muscle mass, and other related outcomes in older adults with sarcopenia [25, 26]. Nevertheless, original intervention studies conducted in nursing home settings or specifically targeting the oldest-old remain scarce. Moreover, the standard standing forms of these exercises may remain challenging for the oldest-old, especially for those with marked mobility limitations or a pronounced fear of falling [27].

Although substantial clinical evidence supports the effectiveness of exercise in the management of sarcopenia, much of this evidence has been generated under highly controlled experimental conditions, with limited consideration of implementation in real-world settings such as nursing homes [28]. This gap between efficacy and applicability has prompted calls for a shift in research priorities, emphasising the optimisation of exercise prescriptions and the promotion of long-term adherence [29]. In institutional care environments, intervention success depends not only on clinical efficacy but also on operational feasibility, safety, and the capacity to sustain participant engagement. Accordingly, effective programmes are those that can capitalise on existing facilities and staff resources, minimise dependence on specialised equipment or external expertise, and integrate smoothly into routine care workflows [30].

Against this background, the present pragmatic trial evaluates a caregiver-led exercise programme that integrates modified Baduanjin with resistance training in oldest-old nursing home residents with sarcopenia. Using a cluster-randomised design and multimodal assessment, the study examines the comparative effectiveness of these interventions while simultaneously exploring underlying biological mechanisms and implementation feasibility. By prioritising practicality and sustainability, this programme is intended to provide an exercise framework that can be readily adopted by other long-term care facilities facing similar resource constraints and resident needs.

## Methods

### Sample size determination

The sample size was estimated using G*Power version 3.1 (Heinrich Heine University Düsseldorf, Germany) based on the composite sarcopenia Z-score. A previous comparable trial reported a large intervention effect on sarcopenia Z-score (SMD = 1.40) [31]. With 80% power, a Bonferroni-adjusted two-sided α of 0.0167, and ANCOVA adjustment for baseline sarcopenia Z-score, 16 completers per group are required in an individually randomized design, corresponding to 64 completers in total. To account for cluster randomization at the residential-building level, the sample size was inflated using the adjusted design effect formula, DE = 1 + [m (1 + CV^2^) − 1] × ICC. Based on a recent cluster-randomized trial in senior care facilities using Short Physical Performance Battery (SPPB) as the primary outcome, an intracluster correlation coefficient (ICC) of 0.025 was adopted [32]. A CV of 0.30 was used to account for anticipated variation in cluster size [33]. With 19 clusters, these assumptions yielded an adjusted design effect of approximately 1.12. After allowing for a 30% dropout rate, the sample size was increased to 104 participants, targeting approximately 26 participants per group. Cluster effects will be further addressed using mixed-effects models with random intercepts for residential building and participant.

### Study design and setting

The SCOPE study (Sarcopenia Care in Oldest-old: a Pragmatic Exercise cluster-randomized controlled trial) is a pragmatic cluster-randomized controlled trial, aimed at evaluating the real-world effectiveness and feasibility of different exercise interventions for sarcopenia in nursing home residents aged 75 and above. A total of 104 participants will be randomized into one of four groups: (1) Control Group (CON), (2) Modified Baduanjin Group (MBG), (3) Resistance Training Group (RTG), and (4) Combined Exercise Group (CEG).

A flow diagram of the trial is presented in Fig. 1. The SCOPE study will begin with continuous screening for sarcopenia following the Asian Working Group for Sarcopenia (AWGS) 2019 criteria [34]. Older adults clinically diagnosed with sarcopenia and meeting the eligibility criteria will be enrolled. After a standardized 30-min health education session and subsequent randomization, participants will undergo a 48-week pragmatic group-based exercise intervention within their residential buildings. This pragmatic intervention will be delivered by trained, familiar caregivers using video materials recorded by exercise specialists, with a phased reduction in researcher supervision over time: full on-site supervision during week 1–12, a hybrid model combining on-site and remote supervision during week 13–24, and fully remote supervision during week 25–48. Outcome assessments will be conducted at baseline, week 12, week 24 and week 48, with additional follow-up evaluations at 1 year and 2 years post intervention to examine the maintenance of long-term effects.

**Fig. 1 Fig1:**
[figure not shown]
Flow diagram of the SCOPE study. AWGS, Asian Working Group for Sarcopenia; BIA, Bioelectrical Impedance Analysis; ASMI, Appendicular Skeletal Muscle Mass Index; HG, Handgrip Strength; GS, Gait Speed; 5STS, Five-Time Sit-to-Stand Test; SPPB, Short Physical Performance Battery; CMMS, Chinese Mini-Mental Status; TUG, Timed Up and Go Test; PA, Physical Activity

#### Diagnostic criteria of sarcopenia

Sarcopenia is diagnosed according to the AWGS 2019 criteria (the SCOPE study was designed before the AWGS 2025 definition of sarcopenia was published [35]), which require the presence of low muscle mass in combination with low muscle strength and/or low physical performance [34]:Low muscle mass is defined as an appendicular skeletal muscle mass index (ASMI): < 7.0 kg/m^2^ for males and < 5.7 kg/m^2^ for females, measured via bioelectrical impedance analysis (BIA);Low muscle strength is indicated by a handgrip strength (HG) < 28 kg for males and < 18 kg for females;Low physical performance is characterized by a gait speed (GS) < 1.0 m/s, a five-time sit-to-stand test (5STS) ≥ 12 s, or SPPB score ≤ 9.

#### Inclusion criteria

Age ≥ 75 years;Diagnosed with sarcopenia according to the criteria described above;Able to understand test instructions, complete questionnaires, and perform the required assessments and exercise movements with or without appropriate assistance;Willing to participate in the study, provide written informed consent, adhere to the intervention protocol, and attend follow-up assessments.

#### Exclusion criteria

Severe cardiovascular or cerebrovascular disease, advanced cancer, severe systemic illness, or moderate-to-severe dysfunction of major organs, including the heart, liver, kidneys, or lungs;Lower-limb joint disease, neurological disorder, or functional impairment that prevents safe participation in exercise or required physical assessments;Use within the past 3 months of medications known to substantially affect muscle, bone, or neuromuscular function, such as glucocorticoids, androgens, estrogens, thyroid hormones, or other relevant agents;Regular high-intensity physical exercise before enrollment, defined as ≥ 15 min of vigorous physical activity daily or resistance training at least twice per week for 3 consecutive months;Diagnosed mental disorder or moderate-to-severe cognitive impairment, defined as a Chinese Mini-Mental Status (CMMS) score < 20 (consistent with CMMS severity mapping and cognitive eligibility thresholds used in previous nursing-home exercise trials [36, 37]);Presence of metal or electronic implants that may interfere with body composition assessment or other study examinations.

#### Participant recruitment and screening

Participant recruitment will be conducted in collaboration with the Hangzhou No.3 Social Welfare Institution, the largest nursing home in the region. The institution spans 169 acres and comprises 26 residential buildings with four to six floors each, providing a total capacity of approximately 2,000 beds. The facility serves a population with a mean age exceeding 80 years and is representative of institutionalised older adults in urban China.

To ensure comprehensive outreach, a multi-faceted recruitment strategy will be implemented, including organised informational seminars, systematic distribution of flyers, and prominently displayed posters in residential and common areas. Residents who express interest will be invited to provide written informed consent. A mobile screening team will then conduct on-site assessments directly on participants’ residential floors, with screening supervised by trained researchers and geriatric physicians. Portable equipment will be used to diagnose sarcopenia in accordance with the AWGS 2019 criteria, thereby enhancing accessibility for frail older adults. Final eligibility will be determined on the basis of screening results in conjunction with the study’s predefined inclusion and exclusion criteria.

### Randomization and blinding

Reflecting the real-world setting, a cluster randomization design will be employed, in which entire residential buildings within the nursing home will serve as the unit of randomization. A total of 19 residential buildings will be included, each comprising approximately 4–10 eligible participants. Clusters will be allocated as evenly as possible to the four study groups. The randomization sequence will be generated by an independent statistician using SAS 9.4 (SAS, USA), with allocation concealed from recruitment and assessment personnel until assignment [38]. Baseline imbalance at both the individual and cluster levels will be descriptively assessed and considered in adjusted and sensitivity analyses.

Because of the nature of the exercise intervention, participants, caregivers, and exercise supervisors cannot be blinded to group assignment. However, outcome assessors and data analysts will remain blinded wherever feasible. No routine unblinding procedure is planned because the interventions are non-pharmacological and group allocation will be known to intervention providers after randomization.

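### Nineteen buildings over four groups means a 5/5/5/4 split, so expected arms are about 27/27/27/22, not 26 each; the power cost is modest, but the plan does not say which arm is short

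*Protocol article*

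**What the plan says.** Under Randomization and blinding, the protocol article makes the residential building the unit of randomization: "A total of 19 residential buildings will be included, each comprising approximately 4–10 eligible participants". The allocation rule is one sentence: "Clusters will be allocated as evenly as possible to the four study groups". Imbalance is dealt with after allocation: "Baseline imbalance at both the individual and cluster levels will be descriptively assessed and considered in adjusted and sensitivity analyses".

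Under Sample size determination, the base requirement is given as "16 completers per group are required in an individually randomized design, corresponding to 64 completers in total". It is inflated by a design effect of about 1.12 (ICC 0.025, cluster-size CV 0.30). The last step reads: "After allowing for a 30% dropout rate, the sample size was increased to 104 participants, targeting approximately 26 participants per group".

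Under Statistical analysis, the linear mixed model adjusts for the baseline value of the outcome being analysed and has random intercepts for building and participant.

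**The concern.** The per-group target and the allocation rule do not fit together. The target treats the four groups as equal in size. The rule makes one group a building short and does not say which group that is, or how it is chosen.

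The CV of 0.30 in the design effect allows for buildings of different size. It does not allow for one arm having fewer buildings. Because only the building count is evened out, and buildings hold roughly 4 to 10 eligible residents, the number of residents per arm can drift further apart by chance.

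The Bonferroni-adjusted α of 0.0167 is 0.05/3, which fits three comparisons of an exercise group with control. If control is the four-building arm, the smallest arm enters every one of them. If an exercise group is short, only one of the three is affected.

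**Working it through.** **Inputs** (protocol article, Sample size determination and Randomization and blinding): 19 buildings; 104 residents; 16 completers per group before inflation; ICC 0.025; CV 0.30; dropout 30%; two-sided α 0.0167; SMD 1.40.

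**1. The plan's own figure.** Mean cluster size m = 104/19 = 5.47.
- DE = 1 + [5.47 × (1 + 0.30²) − 1] × 0.025 = 1.124, which agrees with the stated 1.12.
- 16 × 1.12 = 17.9, rounded up to 18 completers per group.
- 18/0.70 = 25.7, rounded up to 26, and 4 × 26 = 104.

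The stated total is reproduced, taking the 16 as given.

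**2. Arm sizes under the stated rule.** 19/4 = 4.75, so the most even split is 5/5/5/4.

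| Arm | Expected residents | Completers (× 0.70) |
|---|---|---|
| Five buildings | 5 × 5.47 = 27.4 | 19.2 |
| Four buildings | 4 × 5.47 = 21.9 | 15.3 |
| Plan's target | 26 | 18.2 |

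**3. How likely is 26 in four buildings?** It needs 26/4 = 6.5 residents per building. The article gives no size distribution, so one was assumed: roughly normal, mean 5.47, CV 0.30, held within 4–10, total fixed at 104. In simulated 5/5/5/4 allocations the four-building arm had median 22 (95% range 17–27) and reached 26 or more in about 8%. The median gap between largest and smallest arm was 8 residents.

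**4. Power.** Two-sample t-test at α = 0.0167, completers divided by 1.12 to give effective sizes, noncentrality d × √[n₁n₂/(n₁ + n₂)]. Two effects are shown because 16 per group is more than SMD 1.40 needs at 80% power (13 per group by t-test). The effect at which 16 v 16 gives exactly 80% is d = 1.20.

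| Comparison (completers) | Effective n | Power, d = 1.20 | Power, d = 1.40 |
|---|---|---|---|
| Equal arms, 18.2 v 18.2 | 16.25 v 16.25 | 0.81 | 0.92 |
| Four v five buildings, 15.3 v 19.2 | 13.7 v 17.1 | 0.77 | 0.90 |
| Five v five buildings, 19.2 v 19.2 | 17.1 v 17.1 | 0.83 | 0.94 |

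The loss against equal arms is about 3 points at d = 1.20 and about 2 points at d = 1.40. A comparison between two five-building arms gains about 2 points.

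**5. Baseline severity.** For two arms of 27.4, the SD of the difference in standardized baseline means is √[DE × (2/27.4)].
- DE = 1: SD 0.27, so a difference above 0.3 SD has a chance of about 27%.
- DE = 1.12: SD 0.29, chance about 29%.

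Nearly all of this comes from small arms; clustering at the plan's ICC adds 2 to 3 points.

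**The case against.** The article says approximately 26, and calls it a target. At 4–10 eligible residents per building, four buildings could hold 16 to 40. A reader might infer from the arithmetic that 26 per group is impossible. The documents do not support that: it is unlikely under ordinary allocation of 104 residents, and the figure of 8% depends on an assumed size distribution.

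A reader might also infer from 15 completers against 18 that the trial is underpowered. That does not follow. Residents missing from one arm are in the other three, power depends on both arms of a comparison, and at the article's own SMD the small-arm comparison stays near 0.90.

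A third tempting reading is that severity imbalance is left to choices made after the data are seen. For the baseline Z-score this is wrong: the sample-size section plans "With 80% power, a Bonferroni-adjusted two-sided α of 0.0167, and ANCOVA adjustment for baseline sarcopenia Z-score", and the analysis section puts the baseline outcome value in the primary model. The sentence on imbalance can leave open only further covariates.

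Finally, the article is condensed. Beyond the allocation rule it says only: "The randomization sequence will be generated by an independent statistician using SAS 9.4 (SAS, USA". It does not say that simple randomization is used, and a restriction may be set out in the full protocol. Silence on stratification is therefore not counted as a fault here.

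All four objections stand. What they leave is the mismatch between two stated items, the equal per-group target and a rule that evens only the building count, and the unnamed short arm.

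**Conclusion.** The point holds in limited form. The 5/5/5/4 split follows from the stated rule alone. The expected arm sizes of about 27/27/27/22 (about 19/19/19/15 completers) also need the total of 104 and the 30% dropout, both from the article. The power cost is 2 to 3 percentage points for any comparison that uses the four-building arm, and it falls on all three comparisons with control if control is that arm.

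The power figures rest on the plan's ICC of 0.025, a design effect of 1.12, dropout equal across arms and resident-level degrees of freedom. They are best read as the difference between layouts, not as the trial's actual power. Chance imbalance in severity is mainly a matter of small arms and is largely covered by the planned baseline adjustment. The change is worth making because it costs little before allocation and cannot be made by design afterwards.

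**What to change.** 1. In the sample-size section, state the 5/5/5/4 split and restate the expected arm sizes as about 27/27/27/22.
2. Fix control as one of the five-building arms, and say how the four-building arm is chosen among the exercise groups.
3. Where enrolment in the buildings is complete before allocation, draw the allocation at random from those 5/5/5/4 splits that meet a pre-set limit on enrolled residents per arm and, if available, on mean baseline Z-score and sex mix. Name the constraint variables as covariates in the primary model.

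**Cost.** Items 1 and 2 are wording. Item 3 is a small amount of code for the independent statistician who already generates the sequence. Its downside is timing, because screening data must be ready before allocation. The study-design section places randomization after enrolment and the assessment schedule has the Z-score at screening, which suggests that this is feasible. However, screening is described as continuous, and the Discussion allows recruitment in waves. If waves are used, apply the constraint within each wave.
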